### Implementation strategies

The purpose of developing an implementation blueprint is to provide a guide for stakeholders and providers to enhance readiness and support the scale-up of new practices across different sites (20). As such, development of an implementation blueprint is a complex, dynamic, and collaborative process that engages members across three primary categories: (1) those responsible for implementing the new practice (i.e., providers, supervisors); (2) those who have a role in supporting the new practice and/or removing barriers to its implementation (i.e., providers, supervisors, clinical practice managers); and (3) those who would benefit from implementing the new practice (i.e., patients, providers) (15, 21). The CAB will be convened to operationalize the strategies specific to the local context and contribute to refining the implementation blueprint to maximize site-specific success. Implementation strategies for the blueprint will be selected based on contextual determinants identified in Phase 1 using the i-PARIHS framework (22) and the Implementation Strategy Supplemental Tool (23). A written implementation blueprint document will be developed with operational details for each implementation strategy using the Action, Actor, Context, Target, Time (AACTT) framework (24) to identify the setting, specific action steps, persons responsible, and timeframe to enhance replicability of the blueprint in future investigations across a variety of sites (15). The finalized blueprint will include a tailored manual of procedures (MOP) to support implementation of the practice change. This MOP will include the local leadership and stakeholder teams, identified barriers and facilitators to implementation, recommended implementation strategies, and specific action items and team activities required to support implementation. Activities to support implementation will be displayed using the Implementation Research Logic Model (25) and will include a phased timeline that aligns with common phases of implementation and incremental outcome metrics (26). The implementation blueprint will be deployed at each site prior to initiating Phase 4. Following study completion, the implementation blueprints will be published open access alongside the primary publications to enhance replicability.

#### Phase 4

The goal of Phase 4 is to test the effect of the implementation blueprint on clinical practice patterns with regard to obtaining head CTs for patients who meet the study's inclusion/exclusion criteria across the three enrolling sites. Approximately 140 patients with presenting GCS scores between 13 and 15 will be enrolled across the three sites. The primary endpoint of Phase 4 (to be compared with the outcome of Phase 2) is the rate of head CTs completed in enrolled patients. The secondary endpoint of this phase is the rate of head CTs completed in enrolled patients with negative POC whole blood test results. We will also evaluate if the implementation blueprint has impacted baseline perceptions of facilitators and barriers and related implementation outcomes (i.e., adoption, appropriateness, acceptability, decisions, and feasibility) has shifted provider's perspectives on the test by having those who completed Phase 1 surveys (e.g., Mi-PARIHS) complete the surveys again.

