### Current work

Despite receiving FDA clearance, recognition in national news campaigns, and electronic distribution of test information, ED providers do not routinely utilize this POC whole blood TBI test when evaluating patients with suspected mTBI or determining the need for CT scans. Others have identified additional barriers to routine use. These include entrenchment of CT scans as standard of care, narrow indication of clinical use (FDA approval limited to mTBI patients to rule out the need for a head CT scan), no recommendation yet in clinical guidelines, integration concerns with electronic health records, absence of a current procedural terminology code, and lack of education/awareness about the test and its cost-effectiveness (8–10). To address identified barriers, additional data on clinical effectiveness are needed to determine impact on patient and health system outcomes. In particular, there are no data to indicate other potential uses of the test to predict clinically relevant outcomes beyond ruling out head CT, such as ED length of stay and the incidence of return ED visits. In parallel, there is also an ongoing need to better understand contextual barriers to routine use among frontline clinicians. Therefore, the objective of this study is to identify determinants for routine use of the POC whole blood TBI test within ED settings and to evaluate impact on clinical and health system outcomes.

Each phase of the study will aim to do the following:
Phase 1: Evaluate determinants for routine use of the POC whole blood TBI test by assessing acceptability, adoption, appropriateness, and feasibility of the test at the organizational and provider level for each site and determine how these factors interplay with patient perspectives and knowledge to influence implementation of the test.Phase 2: Evaluate the effectiveness of the POC whole blood TBI test in determining the need for a head CT scan in approximately 140 patients with a Glasgow Coma Scale (GCS) scores of 13–15 in three Level 1 trauma center EDs (∼47 per site) while assessing secondary outcomes with clinical implications (i.e., reduction in ED length of stay and predictive utility for ED revisits for the same injury).Phase 3: Develop a site-specific implementation blueprint for use of the POC whole blood TBI test in determining the need for a head CT scan.Phase 4: Pilot test the implementation blueprint in approximately 140 patients with GCS scores of 13–15 in the ED (∼47 per site).

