The Decisional Conflict Scale (DCS) will be used to assess factors influencing the decision-making processes of providers when deciding between use of the POC whole blood TBI test and CT scanning (12). The DCS measures five dimensions of decision-making, evaluating uncertainty, lack of information, unclear values, lack of support, or ineffective decision-making. The acceptability of intervention measure (AIM) (13) is a five-item measure evaluating the perception among implementation stakeholders that a given practice is agreeable or satisfactory. This tool will assess providers’ perspectives on how acceptable the POC whole blood TBI test is for assessing need for CT and determining the plan of care for patients presenting with mTBI. The AIM has excellent structural and known-groups validity as well as test–retest reliability [intraclass correlation coefficient (ICC) = 0.82] (13). The Intervention Appropriateness Measure (IAM) will also be administered to assess baseline perceptions of the appropriateness of the POC whole blood TBI test (13). The IAM is a five-item measure evaluating the perceived relevance of the test for a given setting. The IAM has excellent structural and known-groups validity as well as test–retest reliability (ICC = 0.94) (13). Adoption will be evaluated by the Adoption of Information Technology Innovation (AITI) (14), a 25-item instrument designed to study adoption of new technologies. The scale has excellent reliability and validity metrics (15). The Williams Intention to Adopt Measure (WIAM) will also be used to evaluate adoption (16). The WIAM will be adapted to the current study to understand the willingness of ED providers to adopt the POC whole blood TBI test. This is a five-item measure where the provider will answer if they have spoken with colleagues about experiences with the POC whole blood TBI test; whether they intend to use the POC whole blood TBI test at each visit; whether they have attended trainings, workshops, or other learning sessions focused on the POC whole blood TBI test; and whether they have searched the literature about point-of-care blood tests for TBI for use with patients. The provider will be asked to rate their intended use of the POC whole blood TBI test across the next 10 patients seen in the ED. The WIAM uses a seven-point scale, ranging from 1 (strongly disagree) to 7 (strongly agree), except for the final question, which ranges from 0 to 10. The WIAM has some of the best psychometric properties among adoption measures (16). Lastly, feasibility will be assessed at baseline using the Feasibility of Intervention Measure (FIM) (13). The FIM is a five-item measure which evaluates the extent to which an assessment can be successfully carried out within a given clinical setting. The FIM has excellent structural and known-groups validity, as well as test–retest reliability (ICC = 0.87) (13).

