
#### Phase 2

The goal of Phase 2 is to enroll approximately 140 patients across the three enrolling site EDs to establish current clinical practice patterns with regard to obtaining head CTs for patients who meet the study's inclusion/exclusion criteria. Prior to initiating patient enrollment, site principal investigators will brief emergency medicine and trauma faculty about the research study, the POC whole blood TBI test, and how to interpret the test results. The intent of this phase is to establish early stakeholder engagement and obtain feedback from frontline clinicians that will inform development of the implementation blueprint in Phase 4.

Timeline of participant outcome assessments can be viewed in Table 1. The primary endpoint of this phase is the rate of head CTs completed in enrolled patients. The secondary endpoint of this phase is the rate of head CTs completed in enrolled patients with negative POC whole blood test results. These primary and secondary endpoints were selected to match the FDA's framing of clinical benefit and to be directly comparable to ongoing and completed studies evaluating utility of blood biomarkers for CT utilization in the ED (6, 17–19). Additional secondary outcomes include ED length of stay (in minutes), return to ED for the same injury within 2 weeks of first ED presentation (yes/no), Military Acute Concussion Evaluation-2 (MACE-2) results, Neurobehavioral Symptom Inventory (NSI), and two customized surveys about knowledge of mTBI and knowledge of the effects of radiation exposure in healthcare settings. ED length of stay can be extracted from the electronic medical record by research personnel, as presentation and discharge from the ED are timestamped. The MACE-2 is a multimodal tool which assesses clinical signs of TBI, incident description, signs, symptoms, medical history, a brief cognitive exam, neurological exam, and modified Vestibular Ocular Motor Screening (VOMS). The MACE-2 takes approximately 15 min to complete. The NSI is a 22-item scale of TBI symptoms since the time of injury.

**Table 1 T1:** Timeline of patient participant outcome assessments.

Outcome	Enrollment	Two-week follow-up
Military Acute Concussion Evaluation—2	X	
Neurobehavioral Symptom Inventory	X	X
Traumatic brain injury knowledge	X	
Radiation exposure knowledge	X	
Quality of Life After Brain Injury Overall Scale		X
Follow-up care survey		X

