##### Secondary outcome comparison

ED length of stay (in minutes) will be compared between patients who only received the POC whole blood TBI test and those who received the POC whole blood TBI test and a head CT scan using an analysis of covariance model including enrollment site as a covariate. This analysis will be conducted only for participants with a negative POC whole blood TBI test to control for clinical severity of the injury. Differences in these rates following implementation will be evaluated using the same approach (both for the overall cohorts and those with a negative POC whole blood TBI test only). An exploratory receiver operating characteristic AUC analysis will be conducted to differentiate patients who return to the ED for evaluation of the same injury within 2 weeks from those who do not, using whole blood GFAP and UCH-L1 as predictors.

To evaluate the effect of the implementation blueprint on perspectives regarding determinants and implementation outcomes, Mi-PARIHS domain scores will be compared pre- and post-implementation using repeated measures general linear model, including site as a covariate. Secondary comparisons will be made for implementation outcomes (e.g., AIM, FIM, and DCS).

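### The change in provider surveys from Phase 1 to Phase 4 is credited to the blueprint, although all or part of Phase 2 lies between the baseline survey and blueprint deployment

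*Protocol article*

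**What the plan says.** All references are to the protocol article.

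- **Baseline.** Methods, Phase 1, surveys ED healthcare providers with the Mi-PARIHS (primary measure of that phase), the DCS, AIM, IAM, AITI, WIAM and FIM. It treats this as the starting value; for example, "feasibility will be assessed at baseline using the Feasibility of Intervention Measure".
- **What follows.** Methods, Phase 2, states that before patient enrolment "site principal investigators will brief emergency medicine and trauma faculty about the research study, the POC whole blood TBI test, and how to interpret" the results. It adds: "The intent of this phase is to establish early stakeholder engagement and obtain feedback from frontline clinicians". About 140 patients are then enrolled, roughly 47 per site, with the test in use.
- **Blueprint.** It is designed in Phase 3 from the Phase 1 determinants and the Phase 2 feedback and practice patterns. It is deployed at each site before Phase 4 begins (Implementation strategies).
- **Second survey and its purpose.** Methods, Phase 4: "We will also evaluate if the implementation blueprint has impacted baseline perceptions of facilitators and barriers", and this is done "by having those who completed Phase 1 surveys (e.g., Mi-PARIHS) complete the surveys again".
- **Analysis.** Under Secondary outcome comparison, the stated aim is the effect of the blueprint on determinants and implementation outcomes, and "Mi-PARIHS domain scores will be compared pre- and post-implementation using repeated measures general linear model", with site as a covariate. AIM, FIM and DCS are named among the secondary comparisons.

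The article describes no provider survey between Phase 2 and deployment, and no group of providers who do not receive the blueprint.

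**The concern.** The survey contrast is labelled a blueprint effect, but its interval holds more than the blueprint. The protocol gives its own reasons to expect that Phase 2 could move some scores. Among the known barriers to use, Current work lists "lack of education/awareness about the test and its cost-effectiveness". Preliminary work reports that physicians who ordered CT despite negative biomarkers cited unfamiliarity with the test. The briefing addresses exactly this. Some WIAM items ask whether the provider has talked with colleagues about the test or attended teaching on it. A provider who attended the Phase 2 briefing could truthfully score higher on such items before any blueprint existed.

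What is at stake is a secondary conclusion with practical use. The article makes the published blueprints its primary deliverable, for other EDs to adapt, and plans a hybrid type III trial from these data. If part of a survey gain came from the briefing or from using the test, other sites would credit it to the blueprint.

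**Working it through.** The article gives no sample size, effect size or expected change for the surveys, so there is no planned figure to reproduce. The power calculation concerns head CT proportions only and does not bear on this point. The check is structural.

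**Step 1. Order of events, from Current work, Study design and the Methods text for each phase**

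| Event | Phase | Provider survey? |
|---|---|---|
| Determinant and implementation measures | 1 | Yes, S1 |
| Faculty briefing on the test and its interpretation | 2, before enrolment | None described |
| Test used in about 47 patients per site | 2 | None described |
| Blueprint designed | 3 | None described |
| Blueprint deployed | before Phase 4 | None described |
| About 47 further patients per site; surveys repeated | 4 | Yes, S4 |

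**Step 2. What the contrast contains**

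S4 − S1 = (Phase 2 effect) + (blueprint effect) + (time trend)

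There is one observed difference and three unknown components. Site as a covariate does not help, because every site goes through the same sequence. Separating the first two components needs either a survey between them or a comparison group, and the article describes neither.

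**Step 3. Range of the Phase 2 share**

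Let f be the fraction of S4 − S1 that arises from Phase 2, and ignore time trend. The blueprint part is then (1 − f) × (S4 − S1).

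- f = 0: the whole change belongs to the blueprint, and the stated attribution is right.
- f = 1: none of it does.
- f < 0 (Phase 2 moved scores against the overall change): the contrast understates the blueprint.

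Nothing in the article narrows f.

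**Step 4. How firm the order is**

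The phase numbering and the word baseline put S1 before the briefing, but two places blur this. The Results paragraph of the Abstract has determinants evaluated at the same time as the first 140 patients are studied. The Statistical analysis section places the patient results of the first cohort under its Phase 1 heading and the determinant measures under its Phase 2 heading, the reverse of the Methods.

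- If the phases are sequential, all of Phase 2 lies inside the survey interval.
- If they overlap, some baselines may follow the briefing. The rest of Phase 2 still lies inside the interval, to a different extent for each respondent.
- The problem would disappear only if every baseline were completed after Phase 2 had ended. No section says that.

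**Step 5. Comparison with the CT endpoint**

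The primary comparison sets the Phase 2 cohort against the Phase 4 cohort. The briefing precedes Phase 2 enrolment, so it comes before both cohorts and does not fall between them.

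**The case against.** The strongest defence is that Phase 2 engagement is part of the implementation strategy. The blueprint draws on Phase 2 feedback, its development is described as collaborative with providers, and the analysis is worded as pre- versus post-implementation. On that view Phase 1 is a legitimate starting point for a hybrid type II study. This stands as a defence of the timing. It does not rescue the attribution, because the Phase 4 text and the analysis section both name the blueprint as the cause.

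Several stronger readings are tempting, and the article does not support them:

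- **Long exposure.** A reader might infer months of exposure before deployment. No phase duration is given, only the patient numbers.
- **Every respondent exposed.** The briefing is for emergency medicine and trauma faculty, whereas the survey is of ED healthcare providers and is summarised by stakeholder type. The groups need not coincide. The test is run by trained personnel who may not be respondents, and how many tested patients any respondent treats is unknown.
- **Upward bias on all scales.** This is plausible for awareness and training items. First-hand use can also expose workflow problems, and the article itself lists electronic health record integration as a concern. Mi-PARIHS or FIM scores could therefore fall.
- **A fixed overstatement factor.** The ratio 1/(1 − f) can be computed for any assumed f, but no value of f has support in the article. Equally, a blueprint with no effect would appear beneficial only if the earlier change was positive and detected.
- **A broken link between survey change and CT change.** The two contrasts do start at different points, but no analysis linking them is planned.

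**Conclusion.** The point holds as a problem of attribution in a secondary outcome. As written, the analysis would report the combined effect of the briefing, Phase 2 exposure, the blueprint and any time trend as the effect of the blueprint alone. The size of the error cannot be calculated, and its direction is not established beyond the awareness and training items.

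The conclusion rests on two assumptions: that at least part of Phase 2 follows the baseline survey, which the Methods imply but the article does not date exactly; and that at least some respondents were briefed or met the test in use. It does not depend on every respondent having been exposed. Later analysis cannot recover a survey wave that was not collected, so this is not a matter that an SAP could settle. The primary CT result is not affected by this problem. The change is worth making before Phase 2 ends, but it does not threaten the main conclusion of the trial.

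**What to change.** 1. State when the Phase 1 survey is completed relative to the Phase 2 briefing and enrolment. Bring the Abstract and the Phase 1 and Phase 2 headings of the Statistical analysis section into line with the Methods. This costs only an edit.
2. Describe the Phase 1 to Phase 4 survey change as the effect of the whole programme (briefing, Phase 2 exposure and blueprint), in both the Phase 4 text and the Secondary outcome comparison. This costs nothing beyond a narrower claim.
3. If a blueprint-specific claim is to be kept, repeat at least the Mi-PARIHS and the short measures (AIM, IAM, FIM, WIAM, DCS) once at the end of Phase 2, before deployment. Use that wave as the pre value, keep the Phase 1 wave for designing the blueprint, and report the change between those two waves separately. The protocol already presents the Mi-PARIHS as a tool for repeated administration. The cost is one more electronic survey that includes a 34-item instrument, with some burden and possible attrition among respondents. Time trend after that wave would still be part of the contrast, since there is no comparison group.

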### Sample size

#### Power analysis

The primary endpoint of the overall study is to evaluate the effect of the implementation blueprint by comparing the proportion of patients receiving head CTs in the first patient cohort (enrolled in Phase 2) with the second patient cohort (enrolled in Phase 4). Given that 100% of patients in our pilot study received a head CT scan (regardless of POC whole blood test results), we expect the proportion of head CT scans to be high for Phase 2 enrollments. We hypothesize that a 20% reduction of head CT scans in Phase 4 would be possible after the implementation of the blueprint, representing a clinically meaningful reduction.

A power analysis was conducted using a two-tailed Fisher's exact test for two independent groups, using the proportions of 95% for Phase 2 and 75% for Phase 4, an alpha of 0.01, and power of 0.99. The analysis yielded a sample size of *n* = 140 in Phase 2 and *n* = 140 in Phase 4, with a total of 280 participants with mild TBI. G*Power (version 3.1.9.6) was used for the power analysis.

### Data management and analysis

Research data will be entered into a REDCap database managed by the University of Pittsburgh. Direct personal identifiers will be stored separately in REDCap and replaced with unique identification numbers for the purpose of protecting the identity of the source(s); the original identifiers will be retained in such a way that they can be traced back to the source(s) by someone with the linkage code. The linkage code will have restricted access to approved study team members at each participating site and will not be available to any external entity. To further protect against risk to confidentiality, any information with direct identifiers (i.e., names or other identifying information) will be kept separately and accessible only to approved research team members.

### Statistical analysis

Normality will be assessed for all outcomes, and appropriate transformations will be made to ensure that statistical assumptions are met prior to conducting all analyses. Statistical significance for these evaluations will be set at *p* < 0.05, and Bonferroni corrections will be applied to all analyses for multiple comparisons.

#### Phase 1

For Phase 1, descriptive statistics will be calculated for POC whole blood TBI test results, including the rates of elevated vs. non-elevated values, rates of CT scans ordered, and rates of return ED visits for the same injury within 2 weeks in the first group of 140 ED patient participants. Whether or not the patient returned will be self-reported at the 2-week follow-up survey sent to the participants. ED length of stay (in minutes) will be compared between patients who only received the POC whole blood TBI test and those who received the POC whole blood TBI test and a head CT scan using an analysis of covariance model, including enrollment site as a covariate. This analysis will be conducted only for participants with a negative POC whole blood TBI test to control for clinical severity of the injury. An exploratory analysis using receiver operating characteristic area under the curve (AUC) will be conducted to differentiate patients who return to the ED for evaluation of the same injury within 2 weeks from those who do not, using whole blood GFAP and UCH-L1 as predictors. Approximately 5% of patients diagnosed with TBI and GCS scores of 13–15 in the ED return to the ED within 72 h of discharge for TBI evaluation (27). The expected event rate would yield seven returns to the ED for the Phase 2 cohort of *n* = 140, which is lower than the standard expectation of 10 events per predictor. Statistical significance for these evaluations will be set to *p* < 0.05.

#### Phase 2

For Phase 2, descriptive statistics for all determinant measures will be calculated. Items from the Mi-PARIHS will be plotted as originally described for visual inspection of the weakest domains. These statistics will be calculated by site and by stakeholder type to facilitate presentation to the CAB and to inform development of the implementation blueprint.

Phase 3 will not have a corresponding statistical analysis because it is entirely dedicated to the development of the site-specific blueprints.

#### Phase 4

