### Community advisory board

A diverse community advisory board (CAB) of stakeholders related to the implementation of the POC whole blood TBI test in the ED will be assembled to assist in Phases 3 and 4. The CAB will be assembled by the University of Pittsburgh's Clinical Translational Science Institute and will include representatives from each enrolling institution to provide site-specific context. Members of the CAB will include (from each site) recent acute mTBI patients in the ED, hospital administrators, ED physicians, ED staff (e.g., medical assistants), ED nurses, and the team's implementation scientist. The CAB will be assembled two times per year during the study period for a virtual meeting. Objectives of the initial meetings will be to brief the CAB on the final study design, outcomes (and what they mean), and objectives for conducting the study. Input from the CAB will be integrated into study procedures prior to the initiation of the study. Objectives of the subsequent meetings will be to brief the CAB on findings from Phases 1 and 2, and to discuss determinants (in their view) of successful implementation of the test.

#### Phase 1

The goal of Phase 1 is to establish determinants of use for the POC whole blood TBI test for each enrolling site's ED. To accomplish this goal, we will survey ED healthcare providers to identify determinants of routine use, decision-making processes, and perspectives on acceptability, appropriateness, adoption, and fidelity.

To evaluate determinants of routine use, the Mobilizing Implementation of iPARIHS Facilitation Planning tool (Mi-PARIHS) will be administered as the primary outcome measure for this phase. The Mi-PARIHS is a 34-item tool which supports users in their assessment of the innovation, context and recipient constructs, development of a tailored facilitation plan, and repeated use over time to evaluate the effectiveness of facilitation strategies. Each question is rated on a five-item Likert scale to identify barriers and facilitators/enablers for the innovation being evaluated, where −2 indicates a barrier and +2 indicates a facilitator for that aspect of implementation. In alignment with the i-PARIHS framework, domain scores are summed across innovation, recipients, and context items where higher scores indicate more facilitators/enablers and lower scores indicate more barriers.

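### The plan fixes plain Bonferroni for multiple comparisons; Holm's step-down procedure keeps the same 0.05 family-wise bound and would give the secondary provider comparisons somewhat more power

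*Protocol article*

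**What the plan says.** The opening of the Statistical analysis section sets the level and the multiplicity method for the whole document: "Statistical significance for these evaluations will be set at *p* < 0.05", and "Bonferroni corrections will be applied to all analyses for multiple comparisons". No step-down variant is named, so the plain reading is single-step Bonferroni, with each of m tests held to 0.05/m. The document does not say which tests form a family.

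The clearest set of parallel tests is the provider survey comparison. Under Secondary outcome comparison, "Mi-PARIHS domain scores will be compared pre- and post-implementation using repeated measures general linear model, including site as a covariate". The Phase 1 methods say that "domain scores are summed across innovation, recipients, and context items", which gives three scores. The same paragraph of the analysis plan adds an open list: "Secondary comparisons will be made for implementation outcomes (e.g., AIM, FIM, and DCS". The Phase 4 methods describe these as "related implementation outcomes (i.e., adoption, appropriateness, acceptability, decisions, and feasibility", to be measured by "having those who completed Phase 1 surveys (e.g., Mi-PARIHS) complete the surveys again". Besides Mi-PARIHS, Phase 1 administers six instruments: DCS, AIM, IAM, AITI, WIAM and FIM. No provider sample size, expected change or simultaneous confidence interval is given.

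**The concern.** Bonferroni holds every test in a family to 0.05/m, however many of the others have already been rejected. Holm uses 0.05/m for the smallest p-value, then 0.05/(m-1) for the next, and so on, stopping at the first failure. For reject-or-not decisions under a common family-wise bound, Holm is never worse. All the provider scales ask about the same blood test, so several could plausibly shift together, and that is where Holm gains most. At stake is how many real shifts in determinants and implementation outcomes the study can declare after the blueprint. This is an explicit Phase 4 question in a hybrid effectiveness-implementation design.

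**Working it through.** **Inputs from the document.** Family-wise level 0.05 (Statistical analysis). Three Mi-PARIHS domain scores and six other instruments (Phase 1 methods). Taking one total per instrument, 3 + 6 = 9 scores from seven instruments.

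**Assumed inputs.** Two-sided tests, one family, one DCS total, the number of providers, the size of the change and the correlation between scores. None of these is in the document.

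**The plan's own power figure.** The only one concerns the primary endpoint: 95% against 75%, two-tailed Fisher's exact test, alpha 0.01, 140 per cohort, power 0.99. Exact enumeration gives 0.988, so it reproduces. At the harshest level considered here, 0.05/9, the same test still has power 0.980. The choice of procedure therefore hardly touches the primary comparison.

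**Thresholds for m = 9.**
- Bonferroni: 0.05/9 = 0.0056 for all nine scores.
- Holm, on ordered p-values: 0.05/9 = 0.0056, 0.05/8 = 0.0063, 0.05/7 = 0.0071, and so on up to 0.05/1 = 0.05.

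**Why the bound is the same.** Let m0 of the m hypotheses be true nulls. When Holm first rejects a true null, at most m - m0 rejections came before it, so the threshold then is at most 0.05/m0. A false rejection therefore needs some true-null p-value at or below 0.05/m0. The probability of that is at most m0 x 0.05/m0 = 0.05, whatever the dependence.

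**Illustration 1.** 60 providers with both surveys, standardised change 0.4, correlation 0.5 between changes, one-sample t-tests on change scores (simulation):

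| Family | Truly shifting | Average power, Bonferroni | Average power, Holm |
|---|---|---|---|
| 9 scores | 3 | 0.59 | 0.61 |
| 9 scores | 6 | 0.59 | 0.65 |
| 9 scores | 9 | 0.60 | 0.72 |
| 3 Mi-PARIHS domains | 3 | 0.74 | 0.82 |

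With all nine shifting, the chance of detecting all nine rises from 0.15 to 0.47. With six shifting and three true nulls, realised family-wise error rises from about 0.016 to 0.032.

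**Illustration 2.** Different assumptions: z-tests, with unadjusted power per test fixed (100,000 simulated sets):
- Nine scores, unadjusted power 80%, correlation 0.5: 51% to 53% (three true), 51% to 56% (six), 51% to 62% (nine).
- All effects true, same settings, smaller families: 66% to 74% (m = 3), 57% to 67% (m = 6), 54% to 65% (m = 7).
- Low end (nine scores, three true, unadjusted power 50%): 20.9% to 21.4% with correlation 0, and 20.8% to 21.6% with correlation 0.5, a gain under 1 point.
- High end (nine true, unadjusted power 90%, correlation 0): 68% to 82%.
- With no true effects, family-wise error is identical: 4.9% at correlation 0 and 4.0% at correlation 0.5. With some true effects, Holm's was at most about 4.3%.
- With all nine true, unadjusted power 80% and correlation 0.5, the chance of at least one rejection is 90.7% under both, because the first Holm step is the Bonferroni step.

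In no simulated data set did Bonferroni reject a hypothesis that Holm did not.

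**The case against.** The strongest reply is that nothing here is wrong. Bonferroni is standard, simple and valid under any dependence, and the outcomes concerned are secondary provider surveys. That stands: the point is about efficiency only. One could add that the adjustment algorithm is detail for an analysis plan. That carries less weight, because the article names the method itself.

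Second, the family of nine is a construction. A reader might infer that the plan sets up one nine-test comparison, but it never does. Mi-PARIHS is the Phase 1 primary measure and could well be a family of three, apart from the secondary scales. The secondary list is open-ended. The plan also notes that "The DCS measures five dimensions of decision-making"; testing these separately would make 3 + 5 + 5 = 13 scores. This objection stands for the size of the gain but not for its direction, since Holm is at least as powerful for any family of two or more.

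Third, a reader might infer that Bonferroni gives up power for nothing. That goes too far. Only the upper bound on family-wise error is shared. Realised error below the bound can rise, and single-step Bonferroni has simple matching confidence intervals. The interval cost is modest here because the plan calls for no simultaneous intervals.

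Fourth, the power figures rest on assumed provider numbers, changes and correlation, and on change-score tests, not the planned repeated measures model with site as covariate. The larger gains need every score to shift. That also stands, so the low-end figures belong beside the high ones.

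**Conclusion.** The point holds as a minor efficiency recommendation for the secondary provider outcomes. The plan commits to a valid procedure that is less powerful than an equally simple alternative with the same 0.05 family-wise bound. Under the illustrative nine-score family (60 providers, change 0.4, correlation 0.5), the average gain per score runs from about 2 points when three scores shift to about 12 points when all nine do. For the three Mi-PARIHS domains alone, all shifting, it is about 8 points. Under less favourable assumptions it falls below 1 point. The gain appears only after a first rejection.

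It would be tempting to conclude that real shifts will go unreported. The document does not support that, because it gives neither provider numbers nor expected changes. What can be said is that some real shifts may be labelled not significant that Holm would have declared.

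**What to change.** In the opening paragraph of the Statistical analysis section, replace the reference to Bonferroni corrections with *the Holm step-down procedure (family-wise 0.05)*. Apply it within each set of comparisons that would otherwise have been Bonferroni-corrected, in particular the Mi-PARIHS domain scores and the other provider instruments. Report Holm-adjusted p-values. Holm, like Bonferroni, needs each set to be listed, so the sets should be written down, and the change made, before Phase 4 provider data are seen.

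The cost is one sentence, with no further data, patients or providers. Confidence intervals that match Holm are less simple, so show unadjusted intervals labelled as such, or Bonferroni intervals beside the Holm-adjusted p-values. Realised family-wise error will rise somewhat when some scores truly shift, but stays at or below 0.05.
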